### Inclusion criteria

In order to be eligible to participate in this study, a subject must meet all of the following criteria:More than 18 years of age.Informed consent.Physically and mentally capable of giving consent for participation and data storage.diagnosed with an aneurysm of the abdominal aorta with a diameter of at least 55 mm (or growth of 5 mm or more in 6 months) suitable for bifurcated endovascular repair through two femoral access sites, without additional access needed.

### Exclusion criteria

Exclusion criteria are indicated as follows:Patients with severe atherosclerosis at the access site (more than 50 % of the circumference of the common femoral artery).Patients with previous common femoral artery surgery.Patients with a documented infection at the time of operation.Patients treated with an aorto-monoiliacal device implanted, followed by a femoro-femoral crossover.Patients with an aneurysm necessitating more than two accesses (brachial or carotid) for repair.

### Recruitment

Patients more than 18 years of age and presenting at the outpatient clinic of participating hospitals, with an indication for bifurcated EVAR will be asked to participate. Patients will be informed about the purpose, and intervention of the study, its duration and the risks. Consent will be obtained with explanation and a signature on the Informed Consent Form. Patients have 1 week to consider their decision.

Withdrawal from the study is possible at any time for any reason and is without further consequences.

### Randomization

Randomization will be performed prior to operation. The operating physician or his/her assistant must draw a blinded envelop to allocate the patient to one of the two groups.

In the first group (group A), surgical access is achieved for the main body of the endoprosthesis. In the second group (group B), the Prostar XL™/Proglide™ device gives passage to the main device.

The allocation will be noted at the case report form (CRF) present in the envelope, which also contains a circular blade of 3 mm diameter, and 3 culture mediums (Thioglycollate medium USP, Mediaproducts, Groningen, Germany). Two cultures are taken after completion of the preoperative checklist and after administration of prophylactic antibiotics (1 g cefazolin, intravenously 15 to 60 min before surgery): one nose culture and one perineal culture is performed with a swab, rotated at the nasal and perineal site. The punch biopsy is collected from the right groin after disinfection, a circular blade of 3 mm is rotated and 2 skin biopsies are harvested. One punch biopsy is stored in formaldehyde; the second punch biopsy is stored in the third culture medium.

The culture media and formaldehyde storages have been coded in advance by the investigator, who prepared the content of the blinded envelop, and these samples will be sent to the laboratory of CERTE in an enclosed addressed envelope.

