**Methods/Design:**

Percutaneous access of the CFA is compared to surgical cutdown in a single patient; in EVAR surgery, access is necessary in both groins in each patient. Randomization is performed on the introduction site of the larger main device of the endoprosthesis. The contralateral device of the endoprosthesis is smaller. When we use this type of randomization, both groups will contain a similar number of main and contralateral devices. Preoperative nose cultures and perineal cultures are obtained, to compare colonization with postoperative wound cultures (in case of a surgical site infection). Furthermore, patient comfort will be considered, using VAS-scores (Visual analog scale). Punch biopsies of the groin will be harvested to retrospectively compare skin of patients who suffered a surgical site infection (SSI) to patients who did not have an SSI.

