### Secondary endpoints

Wound complications in both groups are assessed during the first 30 days postoperatively. Close attention will be paid to hematoma, femoral neuropathy, dehiscence, fluid discharge, stenotic/occlusive complications in the CFA and signs of infection.

When a *Staphylococcus aureus* SSI occurs (as the major contributor to all in the groin), preoperative isolates will be compared to postoperative SSI involved strains.

All patients will score their wound comfort or pain in a validated VAS score 1 day, and 2 weeks after surgery. Outcomes for open femoral versus percutaneous access will be compared.

Percutaneous access of the CFA is expected to inflict less surgical site infections in the groin compared to open surgical cutdown of the CFA. A lower incidence of infections and localized postoperative problems is expected to offset the additional costs of the percutaneous device. Still, the reduction in complaints needs to be quantified.

Follow-up will be performed until 1 year after the operation, according to the definition of a surgical site infection: “if implant (the endoprosthesis) is in place and the infection appears to be related to the operation” [15].

Recent studies suggest that certain patients may be colonized by multiple different *S. aureus* clones [16]. Also, these bacteria may hide intracellularly [17]. In case of a SSI, we hope to identify the initial localization of the causative microorganism. Therefore, preoperative cultures and punch biopsies will be used, respectively, to study the clonality of isolates by genotyping and to identify intracellular bacteria by fluorescence *in situ* hybridization (FISH) and fluorescence microscopy [18].

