## Discussion

Comparison of the incidence of SSIs in one patient may answer (an important part of) the question whether percutaneous closure devices deserve a role in the prevention of SSIs after EVAR. The cost of an SSI is estimated to be between US $10.000, and $20.000 per infection [19]. In pEVAR, a trend was noticed to reduce procedure and hospitalization times [10–12, 20]. The aim of this study is to contribute to the rationale of using percutaneous devices for femoral access in EVAR.

Analysis will be performed on an intention-to-treat basis. When a percutaneous access, for some reason, is not successful, open access will be obtained. Reasons why percutaneous access may not be successful are described in the Statistical Analysis section.

For all participants, cultures of the nose and the perineum will be taken preoperatively. In addition, two punch biopsies from the right groin will be obtained to evaluate the presence of microorganisms in deeper layers of the skin or intracellularly (by culture/molecular methods and PA research). The intention is to compare cultures and SSIs as it becomes more apparent that differences in hostility between bacterial species and/or clones exists [16, 17]. Therefore, the assumption was made, that a SSI does not only develop due to flaws in sterility [21], but also because some bacteria might be able to conceal themselves better in or on their host, than other bacteria. We know that bacteria can hide intracellularly [17, 22], and take over resistance genes from each other. Therefore, it might be interesting to compare *S. aureus* strains not causing SSIs, to those that do cause an SSI.

In conclusion, the PiERO trial is a multicenter randomized controlled clinical trial designed to show the consequences of using percutaneous access in EVAR surgery, when considering surgical site infections. In addition, patient comfort, estimated hospital stay and other wound complications are taken under consideration.

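### Colonisation swabs are taken after the prophylactic antibiotic, and biopsies confined to the right groin leave about half of infected groins without a same-side skin sample

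*Protocol article*

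**What the plan says.** All the sampling instructions stand in the Randomization section of the protocol article.

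- **Swabs.** On timing: "Two cultures are taken after completion of the preoperative checklist and after administration of prophylactic antibiotics". On site: "one nose culture and one perineal culture is performed with a swab".
- **Biopsies.** On side: "The punch biopsy is collected from the right groin after disinfection". On number and size: "a circular blade of 3 mm is rotated and 2 skin biopsies are harvested". One goes into formaldehyde and the other into culture medium.

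The samples have four stated uses.

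- Under Secondary endpoints, for *S. aureus* infections, "preoperative isolates will be compared to postoperative SSI involved strains".
- In the same section: "In case of a SSI, we hope to identify the initial localization of the causative microorganism". Both the preoperative cultures and the biopsies serve this aim.
- The Abstract describes the biopsies as a means "to retrospectively compare skin of patients who suffered a surgical site infection (SSI) to patients who did not have an SSI", and the Discussion gives their purpose as "to evaluate the presence of microorganisms in deeper layers of the skin or intracellularly".
- Under Secondary study parameter(s), nose and perineal colonisation enter the multivariate analysis, as do left/right differences.

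The article gives no reason for swabbing after the antibiotic or for always using the right side. It does not say where in the groin the punches lie relative to the access wound.

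**The concern.** There are two separate problems.

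**Order of swab and antibiotic.** A preoperative culture can serve as a baseline for strain matching, or as a covariate, only if it shows what the patient carried. An antibacterial dose before the swab can turn a carrier's culture negative, and there is no plausible way for it to raise the yield. A carrier recorded as a non-carrier is a misclassified covariate. In a patient who later develops an infection, it is also a lost chance to match strains.

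**Fixed side of the biopsy.** Finding where the causative organism came from is a question about one groin. Technique is randomised by device component, not by side, so the infected groin can be either one. Both punches come from the right, so a left-groin infection has no skin sample from its own site. The punches also place two research wounds in one of the two groins being compared, in a design whose merit is that the groins should differ mainly by technique and device diameter.

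At stake are the secondary microbiology, which will rest on few infections, and some avoidable noise in the primary endpoint.

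**Working it through.** **Inputs.** From Sample size calculation: p1 = 0.068 (open), p2 = 0.001 (percutaneous), 120 patients including 5 % fall-out, and the formula n = 8 × (p1(1 − p1) + p2(1 − p2))/(p1 − p2)². From Study design: 1:1 allocation of technique to main device or contralateral limb.

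**1. The plan's own figure.** n = 8 × (0.063376 + 0.000999)/0.067² = 0.515/0.004489 = 114.7. With 5 % fall-out, 114.7 × 1.05 = 120.5, or 114.7/0.95 = 120.8. The stated 120 is reproduced and is not in dispute.

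**2. Expected infections.** 120 × 0.068 = 8.16 open and 120 × 0.001 = 0.12 percutaneous, in all 8.28.

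**3. Share on the left.** Let q be the probability that the main device goes in on the right, independent of allocation. Then P(open access on the right) = 0.5q + 0.5(1 − q) = 0.5 for any q. If risk does not depend on side or device size, half of the infected groins are on the left: 8.28/2 = 4.14.

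Now let r be an assumed risk ratio, main device versus contralateral limb. Left share = L/(L + R), with L = 0.5(1 − q)r + 0.5q and R = 0.5qr + 0.5(1 − q).

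| q (assumed) | r (assumed) | L | R | Left share |
|---|---|---|---|---|
| any | 1 | 0.50 | 0.50 | 50 % |
| 0.8 | 1.5 | 0.55 | 0.70 | 44 % |
| 0.8 | 2 | 0.60 | 0.90 | 40 % |
| 1 | 3 | 0.50 | 1.50 | 25 % (extreme) |

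**4. Effect of the biopsy wounds on the primary comparison.** Suppose they add an excess infection risk b in the right groin. The documents give no value, so b is assumed over 0.5 % to 2 %. The right groin is the open one in half of the patients and the percutaneous one in the other half, so each technique's rate rises by b/2. The difference stays at 6.7 points and only the variance grows. Power is for an exact two-sided 5 % McNemar test with 120 pairs, groins taken as independent.

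| b | Open | Percutaneous | n by the plan's formula, before fall-out | Power |
|---|---|---|---|---|
| 0 | 6.8 % | 0.1 % | 114.7 | 80 % |
| 0.5 % | 7.05 % | 0.35 % | 123.0 | 76 % |
| 1 % | 7.3 % | 0.6 % | 131.2 | 72 % |
| 2 % | 7.8 % | 1.1 % | 147.6 | 65 % |

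The balance holds only on average. In 120 patients, open access falls on the right in 60 ± 1.96 × √(120 × 0.25), about 49 to 71 patients. At b = 1 %, an imbalance of 71 to 49 shifts the difference by 1 % × (71 − 49)/120 = 0.18 points.

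**5. Swabs.** No yield figure is given, so only the form can be shown. If a share c of patients is colonised and the swab detects a fraction s of them, the recorded share is cs. Among patients recorded as negative, c(1 − s)/(1 − cs) are in fact carriers. Any fall in s raises that fraction and lowers the number of available isolates.

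**The case against.** **The swabs and the Abstract's comparison do not depend on side.** This stands. A reader might infer that the baseline microbiology as a whole misses half of the infections. It does not: nose and perineal isolates serve an infection in either groin, and the Abstract compares skin between patients. Only the same-side localisation aim is affected.

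**The biopsy wounds do not erode the contrast between techniques.** This also stands. Looking at the percutaneous arm alone, a reader might note that its rate at b = 1 % is six times the planned value and infer a bias. The open arm gains the same amount, so the expected difference is unchanged. The left/right term already in the multivariate analysis addresses side as well. Two limits remain. The balance needs the main-device side to be chosen independently of allocation, which the article does not state; and, with about 8 events, adjusting for side cannot be expected to recover the lost precision.

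**Infections at the biopsy site might not be counted.** Partly right. The primary endpoint requires a clinical diagnosis, Southampton Grade III or more and culture confirmation, and the position of the punches is not given. But the endpoint is defined as infection in the groin, and nothing tells assessors to separate the two sites.

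**Sampling after disinfection is deliberate.** Accepted. It fits the search for deep or intracellular organisms and is no part of this point.

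**The loss of swab yield is not quantified and concerns secondary aims.** True. It limits how much weight the point can carry, but not the case for a change of order that costs almost nothing.

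**Conclusion.** The point holds as two limited findings about the secondary microbiology, with a small consequence for the primary endpoint.

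1. Swabbing after the antibiotic can lower culture yield and so misclassify colonisation, both in the strain comparison and in the covariates. The direction is clear; the size cannot be derived from the article.
2. About 4 of 8.3 expected infected groins would have no same-side biopsy. This rests on the planning rates, on 120 patients and on risk that does not depend on side. Under the assumed device and side effects the share is 40 to 44 %, and 25 % in the extreme case.

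The documents do not support reading the biopsies as a bias between open and percutaneous access, or as an error in the sample size. If the punches cause infections at all, the result is added variance: n before fall-out would go from 114.7 to between 123.0 and 147.6 for an assumed excess risk of 0.5 % to 2 %. This rests on 1:1 allocation and on the main-device side being set independently of it.

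**What to change.** - **Swabs.** Take the nose and perineal swabs before the antibiotic is given, and leave the prophylaxis as it is. Flag the patients sampled under the present order in every analysis that uses colonisation or strain matching. At the time of the article 55 patients were included, so up to 120 − 55 = 65 could be sampled in the new order. The cost is one changed line in the sampling instruction, with no additional samples, and a period flag.
- **Biopsies.** Record for each right-groin infection whether it began at the biopsy site. Add a sensitivity analysis of the primary endpoint that sets such infections apart. Limit same-side localisation claims to right-groin infections, and say so in the report. The cost is one item on the case report form and one additional analysis.
- **Not advised.** Taking all biopsies from the edge of the cutdown would match nearly all expected infections, since 0.068/0.069 = 98.6 % fall in the open groin. But it would put every biopsy in the open arm, so that an effect now balanced by allocation would be fully confounded with technique.

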### Blinding

The operating team cannot be blinded for the allocation. Medical staff responsible for control visits and wound evaluation will be blinded for the passage of the main device or the contralateral leg. The scar of the Prostar XL™/Proglide™ device will, however, be smaller. This is an investigator-blinded study.

### Emergency unblinding

To maintain the overall quality and legitimacy of the clinical trial, code breaks should occur only in exceptional circumstances when knowledge of the actual treatment is absolutely essential for further management of the patient. If unblinding is deemed necessary, the investigator should use the system for emergency unblinding through contacting the supervising investigator in writing. The objective database manager, who supervises the codes, is not allowed to give access to the coded patients, unless the supervising investigator ([name]), in a written memo, gives approval.

### Treatment details

#### Participant timelines

Participants are enrolled in the PiERO trial during their preoperative evaluation. Postoperative assessment is performed during the regular outpatient follow up.

#### Concomitant care

In case of an SSI, the wound must be opened, cultured and rinsed with clean water, as considered appropriate according to the treating physician. When infection persists or escalates, oral or intravenous antibiotics are administered. If a second operation is necessary to restrain an infection, this will be registered as an AE.

This trial has no prohibited concomitant medication.

#### Follow-up

Wound control is performed at 1 day, 2 weeks and 6 weeks after operation. Final evaluation will take place at 1 year after the procedure. This evaluation will be carried out for infection of the endoprosthesis, according to the definition [15]. The wound evaluation is carried out using the Southampton Wound Assessment score. Wound complications emerging in between measuring points (1 day, 2 weeks and 6 weeks) will also be recorded.

Three VAS scores (Visual Analog Scale) will be obtained before the operation, 1 day after the operation, and 2 weeks after the operation.

Scores are registered in the CRF (case report form) and collected by the objective database manager (Table 3).

**Table 3 Tab3:** Timeline for participants

	Before operation	1 day after surgery	2 weeks after surgery	6 weeks after surgery	1 year after surgery
VAS score	X	X	X		
Wound assessment		X	X	X	X

VAS, visual analog scale

#### Data management

All forms, diskettes and tapes related to study data will be kept by the database manager. Access to the study data will be restricted. Values will be stored in an Excel sheet. Each additional value added to the database will be stored in consecutively numbered Excel documents, in a security-coded computer. A complete back up of the primary DCC database will be performed weekly and will be stored in locked files (data cannot be altered).

### Statistical analyses

#### Primary study parameter(s)

The occurrence of SSIs in both groups will be compared with a McNemar’s test and proportional hazards regression. Only two measuring points will be defined, but wound complications are expected to emerge also between these measuring points. A Kaplan Meier curve may be used to log incidences according to time. Both groups will be compared using the log rank test.

#### Secondary study parameter(s)

The number of wound complications in both groups will be compared as mentioned previously.

Patient characteristics will be controlled by multivariate analysis with respect to the duration of operation, left/right differences, preoperative bacterial colonization of the nose and the perineum, diabetes mellitus, body mass index, medication, smoking habits and device failure. Although identical groups are examined, we will be able to identify outliers.

Correlations between factors will be estimated using the Pearson correlation coefficient. Proportions of categorical variables are compared using Chi square and Fisher Exact tests, and means of continuous variables are compared using t tests.

The analysis of the primary endpoint (surgical site infection) will be based on an intention-to-treat principle by proportional hazards regression (visualized by Kaplan-Meier survival curves). Intention-to-treat implies that open access because of failed percutaneous access is not excluded from analysis but remains in the percutaneous group. Reasons why percutaneous access may not be successful are inability to obtain access to the arterial lumen with a needle, rupture of the threads of the Prostar XL™ device/2 Proglide™ devices, necessitating open repair and persistent bleeding despite successful use of the Prostar XL™ device/2 Proglide™ devices. The survival analysis is not affected by patient withdrawals (as they will be censored) provided that dropping out is unrelated to prognosis (Table 4). Other outcomes, such as VAS scores 2 weeks post-randomization, may be missing for patients who withdraw from the trial. We will actively seek out reasons for withdrawal and compare the reasons qualitatively.

**Table 4 Tab4:** Number of included patients in the participating centers

Participating center	Number of included patients
- University Medical Center Groningen	13 patients included
- Isala Hospital Zwolle	19 patients included
- Medical Center Leeuwarden	14 patients included
- Wilhelmina Hospital Assen	8 patients included
- Scheper Hospital Emmen	1 patient included
Total:	55 patients included

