## Background

Percutaneous endovascular abdominal aortic aneurysm repair (pEVAR) has been stated to be safe and feasible [1], even though several publications report a substantial number of complications [2–4]. With evolving experience, various risk factors have been identified, including obesity, groin scarring, common femoral artery (CFA) morphology and tortuous iliac arteries [1, 5].

Many current devices successfully close percutaneous punctures of the CFA up to 8 Fr.: such as the Angio-Seal™ (St. Jude Medical, Minnetonka, MN, USA), Mynx™ (AccessClosure, Mountain View, CA, USA), and the Starclose™ device (Abbott Vascular, Redwood City, CA, USA). The Prostar XL™ device (Abbott Vascular) has been used in femoral arteries, after sheaths of 18 to 24 Fr., with high rates of procedural success [1]. Wound infections appear to be absent [3, 6, 7] or few (0.2 %) [8]. In contrast, open femoral access has wound infection rates varying from 6.4 % [9] to 7.3 % [7]. Also, a longer surgery and hospital stay have been reported [10–12]. In percutaneous access, secondary interventions were more commonly seen, compared to surgical cutdown [10, 11]. Still, in suitable patients, this seems to be the only device capable of closing a 20 Fr. percutaneous arterial access site.

Although research has been performed, comparing both techniques, a comparison of both techniques in one patient has never been performed prior to now. Risk factors (obesity, CFA morphology and tortuosity of the iliac arteries) will be equally divided in this study design. Therefore, postoperative complications will mainly depend on the technique used and on the diameter of the device implanted. Also, each patient will be able to compare the result of both techniques by subjective pain sensation or discomfort.

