## Methods/Design

### Study design

In the current study, percutaneous femoral access is compared to open femoral access. Bilateral femoral access is required in each patient treated with a bifurcated EVAR. Therefore, each patient can serve as his/her own control. Randomization is performed for the caliber of the endovascular device (main device versus contralateral extension) that is introduced within the aorta.

The PiERO trial is designed as a randomized, controlled, nonblinded, multicenter superiority trial with two parallel groups and a primary endpoint of wound infection during the 30 days after surgery. Simple randomization will be performed concerning the diameter of the device component introduced in the artery, with a 1:1 allocation.

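### The planned adjustment for device failure (and duration of operation) turns the adjusted technique effect into one for percutaneous access that did not fail, against the plan's own intention-to-treat rule

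*Protocol article*

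**What the plan says.** The article's section Secondary study parameter(s) fixes a list of adjustment factors. The sentence opens with "Patient characteristics will be controlled by multivariate analysis with respect to the duration of operation, left/right differences, preoperative bacterial colonization of the nose", and the last entries in its list are "body mass index, medication, smoking habits and device failure". In all there are nine: duration, side, nasal colonisation, perineal colonisation, diabetes, body mass index, medication, smoking and device failure.

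Two paragraphs later, under the same heading, the primary endpoint is to be analysed by intention-to-treat, meaning that "open access because of failed percutaneous access is not excluded from analysis but remains in the percutaneous group". The reasons given there for failure include failure to enter the artery, rupture of the closure threads, and bleeding that persists although the device was used.

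The section Primary study parameter(s) names McNemar's test, proportional hazards regression and a log rank test, with no covariates. Each patient has one open and one percutaneous groin. What is randomised is which technique carries the main device: "Simple randomization will be performed concerning the diameter of the device component introduced in the artery, with a 1:1 allocation". The Background expects that "postoperative complications will mainly depend on the technique used and on the diameter of the device implanted". Main versus contralateral device is not among the nine factors.

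**The concern.** Device failure is introduced as a patient characteristic, but it is not one. On the natural reading it is an event that follows allocation and can occur only in the percutaneous groin. A model with terms for technique and failure gives the failed groins their own coefficient. The technique coefficient then compares open access with percutaneous access that worked, and the cost of failure, which intention-to-treat deliberately keeps, leaves the estimate. If failed groins are infected more often than the rest, the adjusted result flatters percutaneous access.

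Duration of operation also arises after allocation and can be lengthened by a conversion, so it does not belong in a model of the technique effect either. It is the lesser issue. If it is recorded once per patient, which the article does not state, it is the same for both groins and drops out of a paired comparison.

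**Working it through.** **Inputs from the Sample size calculation section.** SSI risk 6.8 % open (p1 = 0.068) and 0.1 % percutaneous (p2 = 0.001); 120 patients including 5 % fall-out.

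**Plan's own figure.** 8 × (0.068 × 0.932 + 0.001 × 0.999) / 0.067² = 8 × 0.064375 / 0.004489 = 114.7. Then 114.7 / 0.95 = 120.8, or 114.7 × 1.05 = 120.5. The stated 120 is reproduced to within rounding and is not in dispute.

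**Assumptions.** The article gives no failure rate. Let a fraction f of percutaneous groins fail, let failed groins carry the open risk p1, and let the others carry p2. Then:
- intention-to-treat percutaneous risk: q = (1 − f) × p2 + f × p1
- intention-to-treat contrast: p1 − q, and odds(p1) / odds(q)
- failure-adjusted contrast: p1 − p2, and odds(p1) / odds(p2), whatever f is

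| f (assumed) | q | Risk difference, ITT | Odds ratio open vs percutaneous, ITT |
|---|---|---|---|
| 2 % | 0.234 % | 6.57 points | 31.1 |
| 5 % | 0.435 % | 6.37 points | 16.7 |
| 10 % | 0.770 % | 6.03 points | 9.4 |
| 15 % | 1.105 % | 5.70 points | 6.5 |

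The adjusted values are 6.70 points and 72.9 in every row. For f = 5 %: q = 0.95 × 0.001 + 0.05 × 0.068 = 0.00435, and the odds ratio is (0.068/0.932) / (0.00435/0.99565) = 16.7.

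The table takes 0.1 % as the risk without failure. If 0.1 % were already the intention-to-treat risk, failures at the open risk could be at most 0.001 / 0.068 = 1.5 %.

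**No true difference.** Let both techniques have an intention-to-treat risk of 6.8 %, and let failed groins have r times the risk of non-failed ones. The non-failed risk is 0.068 / ((1 − f) + f × r). With f = 10 % and r = 3 this is 0.068 / 1.2 = 5.67 %, and the adjusted odds ratio is (0.068/0.932) / (0.0567/0.9433) = 1.21. Over f = 5 to 15 % and r = 2 to 3, the spurious odds ratio is 1.05 to 1.32 in favour of percutaneous access. At r = 1 it is 1.

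**Patient-level factors.** Colonisation, diabetes, body mass index, medication and smoking are the same for a patient's two groins. In a paired model they have no estimable main effect and cannot confound technique.

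**Room for adjustment.** Expected SSIs: 114 × (0.068 + 0.001) = 7.9, or 120 × 0.069 = 8.3.

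**Main versus contralateral device.** With simple 1:1 randomisation of 120 patients, a split of 54:66 or worse has probability 0.32 and 50:70 or worse 0.08. Assume the main-device groin has 1.5 to 3 times the infection risk. At the plan's rates nearly all the shift comes from the open groins. With rate ratio 1.5 their risks are 8.16 % and 5.44 %, so a 55/45 split shifts the difference by 0.05 × 2.72 = 0.14 points. With ratio 3 they are 10.2 % and 3.4 %, so a 60/40 split shifts it by 0.10 × 6.8 = 0.7 points. The planned difference is 6.7 points.

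**The case against.** The strongest reply is that the list stands under secondary parameters, while the primary comparison is stated separately and without covariates. Nothing ties the nine factors to it. The sentence that follows the list speaks of identifying outliers, which suggests an exploratory look at patient characteristics. This stands as a limit: a reader might infer that the primary intention-to-treat result is undone, and the text does not support that. It does not remove the point, because the article says these factors will be controlled for, and device failure is among them.

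The size is also open to challenge. The failure rates and the risk in failed groins are assumptions, and the odds ratios look dramatic because the reference risk is close to zero. On the risk-difference scale the gap is 0.3 to 0.7 points for 5 to 10 % failure. Both scales should be read together.

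Two stronger readings are tempting. One is that nine covariates against about eight events must overfit. That applies only to an unpaired model of SSI. In a paired model the patient-level factors drop out, and the article does not say which model is meant. The other is that leaving out main versus contralateral device is an error. It is not: that factor is randomised 1:1, so the unadjusted comparison is unbiased in expectation. Leaving it out costs precision and leaves chance imbalance, no more.

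**Conclusion.** The point holds for the adjusted, secondary technique comparison. Controlling for device failure is incompatible with the intention-to-treat rule under the same heading, provided the term means closure-device failure. The direction, towards percutaneous access, depends on failed groins having the higher infection risk. That is plausible, since they are converted to open access, but the documents do not show it. Under the stated assumptions (5 to 10 % failure at 6.8 %), the intention-to-treat odds ratio of 16.7 to 9.4 becomes 72.9, and the risk difference of 6.4 to 6.0 points becomes 6.7. McNemar's test is untouched. The proportional hazards model for SSI is affected only if the list is applied to it, which the article leaves open. The sample size does not change.

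**What to change.** Reword the covariate sentence as follows:
- Define device failure, remove it and duration of operation from every model of the technique effect, and report failures descriptively as an outcome of percutaneous access.
- Make the adjusted technique comparison paired within patient (for example conditional logistic regression), with technique, main/contralateral device and, if events allow, side. Main/contralateral device is optional, as a guard against chance imbalance. With about eight expected SSIs the model must be penalised, kept this small and labelled secondary.
- Keep the patient-level factors for a separate exploratory description of risk factors between patients.
- State that the unadjusted intention-to-treat comparison is the primary one and that the covariate list does not enter the proportional hazards model for SSI.

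The cost is wording. Allocation is noted on the case report form (Randomization section), and side is already one of the planned factors. The change should be dated before outcome data are analysed; the article reports 55 patients included so far.
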